### Relevant concomitant care permitted or prohibited during the trial {11d}

As specified in the eligibility criteria, patients should preferably be treatment-naive (with no recent psychotherapy or medication use) to minimize confounding effects. However, exceptions will be made for cases where patients experience severe dissociation, derealization, or emotional dysregulation that compromises therapy adherence. In such instances, concomitant antidepressant medications may be prescribed by a psychiatrist and will be carefully documented (including dosage and frequency). For patients already taking antidepressants at baseline, these medications will not be discontinued to avoid destabilization. The primary objective in these cases will be to establish emotional stability to enable continued participation in the study protocol. Throughout the trial, patients will receive psychoeducation emphasizing the importance of not initiating any new psychological interventions. These measures are designed to balance scientific rigor with ethical clinical care while minimizing confounding variables.

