### Criteria for discontinuing or modifying allocated interventions {11b}

Since participation in this study is voluntary, patients may discontinue the intervention at any time, as explained during the informed consent process. From a clinical perspective, the study intervention will be discontinued under the following circumstances:Emergence of severe adverse reactions such as sustained dissociation, suicidal ideation, or emotional dysregulation that temporarily make the patient unresponsive to EMDR therapy—in such cases, therapy will pause to focus on resource-building and stabilization before potentially resuming.Severe non-compliance, defined as missing more than four consecutive sessions without contact.Therapist deviation from the given therapy protocol, as identified during mid-therapy fidelity inspections.

At the time of discontinuation, the following data will be collected to assist in planning the selection of future patients:The point in time when discontinuation occurred.The reason(s) for discontinuation, and when possible, the primary endpoint assessment and existing depressive symptom severity.

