### Outcomes {12}

#### Primary outcome

The primary outcome of the study is to study the change in depressive symptom severity. It will be assessed by using the Hamilton Depression Rating Scale-17 [69]. Depression assessments will be conducted at baseline (T01), mid-treatment (T02), end-of-treatment (T03), and follow-up (T04). The primary endpoint for evaluating clinical effectiveness and non-inferiority is the change in depression scores from baseline (T01) to end-of-treatment (T03).

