### Interim analyses {21b}

The study will incorporate two strategically timed interim analyses to monitor trial progress and participant welfare. The first analysis, focused on safety monitoring, will be conducted after the initial cohort of 40 participants completes their mid-treatment assessments. This evaluation will systematically compare adverse event profiles between the online and in-person EMDR groups, with particular attention to clinically significant indicators such as dissociation rates. Should the analysis reveal substantially higher adverse events in either treatment arm—for instance, elevated dissociation occurrences in the online EMDR group—the protocol will be adaptively modified to incorporate additional stabilization sessions for affected participants while maintaining trial continuity.

The second interim analysis, designed to assess efficacy and futility thresholds, will occur when 60 participants (75% of the target sample) have completed their end-of-treatment evaluations. This analysis will employ O’Brien–Fleming statistical boundaries to determine whether the accumulating data demonstrates either compelling evidence of treatment success or insufficient likelihood of achieving meaningful results. For example, if the analysis reveals that online EMDR demonstrates near-equivalent efficacy to in-person delivery—as might be evidenced by merely a 0.5-point difference on the HAM-D-17 scale (*p* = 0.005)—the trial could be responsibly terminated early based on established efficacy. Conversely, should the data suggest minimal probability of ultimately proving non-inferiority, the futility provisions would be activated to conserve resources. These pre-specified analytical checkpoints are integrated into the study design to balance scientific rigor with ethical responsibility and operational efficiency.

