### Methods for addressing non-adherence and missing data {20c}

To account for protocol deviations, primary analyses will employ both intention-to-treat and per-protocol approaches, with the intention-to-treat population including all randomized participants regardless of adherence and the per-protocol population restricted to those completing ≥ 80% of sessions with verified fidelity. For missing data, a tiered strategy will be implemented:Continuous monitoring with initiated outreach after any missed assessment to minimize attrition.Multiple imputation by chained equations using 50 imputed datasets incorporating baseline characteristics, treatment arm, and observed outcome trajectories as predictors.Sensitivity analyses comparing results with pattern-mixture models that assume different missingness mechanisms (missing at random vs. not at random).

For participants who discontinue therapy but complete all outcome assessments, their available data will be included in the mixed-effects models used for longitudinal analyses.

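### T3 depression scores recorded after an antidepressant is started mid-treatment enter the non-inferiority comparison unseparated, and no planned analysis would show whether unequal use moved the result

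*Protocol article*

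**What the plan says.** Four sections of the protocol article bear on this point.

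- **Concomitant care {11d}.** Clients should preferably be treatment-naive, but "exceptions will be made for cases where patients experience severe dissociation, derealization, or emotional dysregulation that compromises therapy adherence". In those cases "concomitant antidepressant medications may be prescribed by a psychiatrist and will be carefully documented (including dosage and frequency". The stated aim is to "establish emotional stability to enable continued participation in the study protocol".
- **Discontinuing or modifying interventions {11b}.** Sustained dissociation and emotional dysregulation are listed among severe adverse reactions; "in such cases, therapy will pause to focus on resource-building and stabilization before potentially resuming".
- **Primary outcome {12}.** "The primary endpoint for evaluating clinical effectiveness and non-inferiority is the change in depression scores from baseline (T01) to end-of-treatment (T03").
- **Non-adherence and missing data {20c}.** "primary analyses will employ both intention-to-treat and per-protocol approaches". Intention-to-treat takes everyone randomised, whether or not they adhered. The second set is the "per-protocol population restricted to those completing ≥ 80% of sessions with verified fidelity". Neither definition refers to medication started after baseline. Multiple imputation and pattern-mixture models are planned for missing scores.

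Under Statistical methods {20a}, non-inferiority is concluded if the upper limit of the 95% interval for online minus in-person lies below 3 HAM-D-17 points.

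**The concern.** An antidepressant acts on the same symptoms that the primary endpoint measures. When one is started between randomisation and T3, the T3 score reflects EMDR plus a drug, and the plan never separates that score from one obtained on EMDR alone.

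In a superiority trial, additional treatment that narrows the gap between arms usually works against the claim. In a non-inferiority trial it works for the claim if it is given more often in the arm that is doing worse. The usual safeguard is to compare intention-to-treat with per-protocol. Here that safeguard is weak, because the per-protocol rule tests only attendance and fidelity, and the medication is given precisely so that the client can carry on. A medicated client who resumes and attends is in both sets with the same score.

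The other planned checks do not fill the gap. Additional analyses {20b} compares the two populations and examines missing-data patterns. The imputation and pattern-mixture models in {20c} apply to scores that are absent, and a score taken after a medication start is present.

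The concern is with starts after randomisation. Medication already in use at baseline is a different matter and is not at issue here.

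**Working it through.** **Inputs from the article**

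- SD of change 8 points, 40 per arm (sample size section {14})
- Margin 3 points; upper 95% limit must lie below it; online minus in-person ({20a}). For this rule to make sense, a positive difference means that online improves less.

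**Inputs not in the article (assumed)**

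- Excess share of clients starting an antidepressant online rather than in person: 10 to 20 percentage points, that is 4 to 8 more clients of 40
- Effect of the drug on the T3 HAM-D-17 score: 3 to 5 points, additive and equal in both arms

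**Step 1. The plan's own figure.** (1.96 + 0.84)² × 2 × 8² / 5² = 7.84 × 128 / 25 = 40.14, stated as 40 per arm. 80 / 0.85 = 94.1, stated as 94. Both reproduce, and neither is disputed here.

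**Step 2. Precision and pass line.** SE = 8 × √(2/40) = 1.789. Half-width = 1.96 × 1.789 = 3.51. The rule passes if the observed difference is below 3 − 3.51 = −0.51.

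**Step 3. Shift from unequal starts.** Shift = (share starting online − share starting in person) × drug effect. The observed difference is centred on the true EMDR-only difference minus this shift. With equal shares the shift is 0. If the in-person share is larger, the shift changes sign and counts against online.

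**Step 4. Error at the margin.** With a true EMDR-only deficit of 3 points, P(non-inferiority concluded) = Φ(−1.96 + shift / 1.789).

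| Excess online | Drug effect | Shift | P(false non-inferiority) |
|---|---|---|---|
| 0 | any | 0 | 2.5% |
| 10 points | 3 | 0.3 | 3.7% |
| 10 points | 5 | 0.5 | 4.6% |
| 20 points | 3 | 0.6 | 5.2% |
| 20 points | 5 | 1.0 | 8.1% |

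Over a wider grid the extremes are 0.05 × 2 = 0.1 point (2.9%) and 0.30 × 6 = 1.8 points (17.0%).

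**Step 5. Who is in which set.** A medicated client with a T3 score is always in intention-to-treat. The same client is in per-protocol only if 80% of sessions are completed with verified fidelity. The adherence section {11c} allows missed sessions to be rescheduled, so a pause need not disqualify, but a client who does not resume will drop out of that set. The article gives no basis for saying how many fall on each side.

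**The case against.** **Left to the SAP.** Handling of post-randomisation medication and the full per-protocol exclusion list are often SAP content, and this is a condensed article. That has some force. However, the article does more than stay silent: it permits the medication, defines both primary populations and lists the sensitivity analyses, and the path falls between them.

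**Intention-to-treat is right as it stands.** Counting scores regardless of added treatment is a legitimate treatment-policy strategy and suits a trial that describes itself as hybrid effectiveness-implementation. This stands, and the analysis should not be changed.

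**Stronger readings.** A reader might infer several things that the documents do not support.

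- *That EMDR caused the destabilisation.* The concomitant-care section states no cause. Only {11b} treats such events as adverse reactions.
- *That more dissociation online is expected.* Interim analyses {21b} does mention "elevated dissociation occurrences in the online EMDR group", but as an example within a sentence covering either arm. It is not a forecast.
- *That both primary analyses always retain medicated clients.* Some will miss the 80% threshold. The first interim analysis also compares adverse events by arm, so an imbalance in the trigger could be seen, although not its effect on the HAM-D-17.
- *That a shift which carries a true difference of 0 to the pass line is an error.* It is not: at a true difference of 0, concluding non-inferiority is correct.

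**Excluding medicated clients from per-protocol.** This is the obvious remedy, but it selects on an event that follows randomisation and is related to outcome. If online had more destabilised clients, removing them would flatter online. The objection stands and shapes the fix.

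**Size rests on assumptions.** True. In the 10-point scenarios above, the error stays below 5%.

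**Conclusion.** The gap is real but conditional. As written, T3 scores after a newly started antidepressant are pooled with all others under intention-to-treat, and under per-protocol for those who meet the session and fidelity rule. No planned analysis would reveal their influence on the primary contrast. The direction is not fixed: the result is biased towards non-inferiority only if starts are more frequent or more effective online, is unaffected if use and effect are equal, and is biased against online if use is heavier in person.

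Under the stated assumptions the chance of a false non-inferiority conclusion at the margin rises from 2.5% to about 3.7–8.1%. That depends on an assumed rate of starts and an assumed drug effect, neither of which the documents supply, and on an additive effect. The documents do not show that online delivery will be declared non-inferior because its clients were medicated. They show that, if this happened, the planned analyses could not tell. This warrants an inexpensive improvement; it does not invalidate the primary analysis.

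**What to change.** In the section on non-adherence and missing data {20c}:

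1. State that intention-to-treat remains a primary analysis and uses T3 scores regardless of antidepressants started after randomisation (treatment policy).
2. Add one sensitivity analysis of the primary contrast in all randomised clients. Set T3 HAM-D-17 scores obtained after a newly started antidepressant to missing, and impute them under a not-at-random (delta) assumption with the pattern-mixture models already planned. Fix the delta values before unblinding.
3. Report the number of antidepressant starts between randomisation and T3 by arm.
4. If a per-protocol set without these clients is wanted, show it as supplementary only, with the selection problem stated.

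In the concomitant-care section {11d}, add the start date to what is documented. The article names dosage and frequency but no date, and the sensitivity analysis needs one.

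The cost is one extra analysis run and one recorded date. Clinical care, the sample size and the non-inferiority rule are unchanged.

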### Provisions for post-trial care {30}

All trial participants will have access to appropriate post-trial care based on their clinical needs. For responders to therapy (defined as ≥ 60% reduction in HAM-D-17 scores), follow-up sessions will be offered to consolidate treatment gains, consisting of two monthly booster EMDR sessions (in-person or online, per their assigned study arm). Non-responding patients will be referred to stepped-care options, including medication management or alternative evidence-based psychotherapies, such as Cognitive Behavioral Therapy, through the network of collaborating psychiatric clinics.

### Outcomes {12}

#### Primary outcome

The primary outcome of the study is to study the change in depressive symptom severity. It will be assessed by using the Hamilton Depression Rating Scale-17 [69]. Depression assessments will be conducted at baseline (T01), mid-treatment (T02), end-of-treatment (T03), and follow-up (T04). The primary endpoint for evaluating clinical effectiveness and non-inferiority is the change in depression scores from baseline (T01) to end-of-treatment (T03).

#### Secondary outcomes

i.Anxiety symptom severity will be assessed by using the Generalized Anxiety Disorder Questionnaire-07 [70]. It will be assessed at baseline (T01), mid-treatment (T02), end-of-treatment (T03), and follow-up (T04).ii.Feasibility, usability, acceptance, and safety of EMDR therapy will be evaluated by client retention rate [71], therapists adherence scale [72], Mobile Mental Health App Usability Questionnaire [73], User Acceptance of Technology Questionnaire [74] and Perceived Online EMDR Safety Scale [75], respectively.

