### Objectives {7}

Against this background and the aforementioned research gaps, the present study has the following three objectives:To develop an adapted DeprEnd EMDR therapy protocol that is culturally and methodologically appropriate for the treatment of major depressive disorder in Pakistan.To assess feasibility and acceptance of the adapted EMDR therapy for its delivery through in-person and online modes in Pakistan.To assess the clinical effectiveness of the adapted DeprEnd EMDR therapy protocol across in-person and online settings.

Table 1 further provides the alignment of research objectives with the theoretical background of the study. The first objective of this study is grounded in theories such as Cultural Sensitivity Theory and the Adaptive Treatment Framework. These theories provide the conceptual basis for two premises: (a) therapies should be adapted both culturally and methodologically to meet the needs of clients and therapists, and (b) guidelines are required to identify the specific cultural and methodological elements to be included in adapted EMDR therapy. The second objective is guided by theories of Technology Acceptance and Therapy Implementation Outcomes. These models emphasize that user acceptance is a critical factor in determining the successful implementation of therapy. Moreover, understanding how users perceive and accept a therapy determines its feasibility. Finally, the third objective is theoretically anchored in the Adaptive Information Processing model, which explains symptom reduction through memory reconsolidation, while the Tripartite Model provides a complementary framework for examining depressive-anxiety symptomatology.

**Table 1 Tab1:** Aligning study objectives and theoretical background

Research objectives	Theoretical basis
To develop an adapted DeprEnd EMDR Therapy protocol that is culturally and methodologically appropriate for treatment of Major depressive disorder in Pakistan	i. Cultural Sensitivity Theory [43] ii. Cultural Competence Theory [44] iii. Adaptive Treatment Framework [45] iv. Behavioral Intervention Model [46]
To assess feasibility, and acceptance of the adapted EMDR therapy for its delivery through in-person and online modes in Pakistan	i. Technology Acceptance Model [47] ii. Therapy Implementation Outcomes Model [48] iii. Medical Research Council Model [49]

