## Hypotheses of study

Since the second phase of this study deals with clinical effectiveness, the following directional hypotheses will be tested:i.The adapted EMDR therapy will demonstrate a high level of feasibility, usability, acceptance, technical operability, and safety when delivered through in-person and online modes.ii.The online delivery of the adapted EMDR therapy is non-inferior to the in-person mode for treating major depressive disorder in Pakistaniii.The adapted EMDR therapy will bring about significant temporal reduction in the major depressive disorder symptoms across in-person and online modes.iv.The major depressive disorder symptoms are reciprocally linked to the comorbid generalized anxiety disorder symptoms in a manner that treatment conditions moderate this relationship.

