### Intervention description {11a}

This trial employs the evidence-based DeprEnd EMDR therapy protocol for depressive disorders [67]. This protocol is specifically optimized for depressive disorders through modifications in:History-taking (focused on depressive triggers vs. trauma),Preparation (enhanced psychoeducation on depression maintenance), andInstallation (targeting depressive cognition reprocessing) [21].

The DeprEnd EMDR therapy protocol has been culturally and methodologically adapted for the Pakistani context, and the full adaptation process has been published elsewhere [42]. In the present trial, both study arms follow the same adapted protocol, differing only in mode of delivery. The intervention will be delivered over 10–14 weekly sessions, depending on individual clinical presentation and treatment response. Each session will last approximately 60–90 min, consistent with standard EMDR therapy practice.In-person EMDR therapy will be delivered by EMDR-certified therapists in selected psychotherapy clinics. Sessions will follow the adapted DeprEnd EMDR protocol using standard face-to-face procedures, including therapist-guided bilateral stimulation and adherence to protocol fidelity requirements.Online EMDR therapy will be delivered via the BilateralBase platform, a validated telehealth system developed in the UK [68]. Therapists and clients will connect synchronously via secure video conferencing using a computer or mobile device. The platform provides visual and auditory bilateral stimulation, real-time therapist guidance, and session structuring consistent with in-person EMDR delivery. Session recordings are enabled for fidelity monitoring, with appropriate consent and ethical safeguards. Apart from delivery modality, the content, session structure, and therapeutic procedures remain equivalent to those used in the in-person arm.

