## Data collection and management

### Plans for assessment and collection of outcomes {18a}

Primary outcomes (depression severity assessed) and secondary outcomes (anxiety symptoms measured) will be collected at four timepoints: baseline (T1), mid-therapy (T2), post-intervention (T3), and 2-month follow-up (T4). All clinical ratings will be administered by trained research assistants who are blinded to treatment allocation. The feasibility and acceptability of the online platform will be evaluated using three validated instruments, as outlined in the protocol. Treatment fidelity and therapist competence will be assessed through both qualitative and quantitative methods, also detailed in the protocol. Data integrity will be ensured through automated checks for missing values and outliers, complemented by audits conducted by the statistical analyst. Any discrepancies will prompt source document verification by an independent monitor or research assistant.

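### Hypothesis (i) claims high usability and acceptance in both delivery modes, but the scales named for them appear to apply to online technology only; the listed safety outcome has the same limit, although adverse events are recorded in both arms

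*Protocol article*

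**What the plan says.** Under Hypotheses of study, hypothesis (i) predicts a high level of "feasibility, usability, acceptance, technical operability, and safety when delivered through in-person and online modes". The second objective, under Objectives {7}, has a similar reach: "To assess feasibility and acceptance of the adapted EMDR therapy for its delivery through in-person and online modes in Pakistan".

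Secondary outcomes then lists five measures and links them, in order, to four constructs (feasibility, usability, acceptance and safety). They are the "client retention rate", a therapist adherence scale, the "Mobile Mental Health App Usability Questionnaire", the "User Acceptance of Technology Questionnaire" and the "Perceived Online EMDR Safety Scale".

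The section on assessment and collection of outcomes {18a} describes a set of instruments by what they evaluate: "The feasibility and acceptability of the online platform will be evaluated using three validated instruments".

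Intervention description {11a} gives the online arm a telehealth platform. For the in-person arm it says: "Sessions will follow the adapted DeprEnd EMDR protocol using standard face-to-face procedures".

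Three other sections bear on the point:

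- Adverse event reporting and harms {22} has treating therapists record and grade all adverse events, without restriction by arm.
- Interim analyses {21b} compares adverse event profiles between the arms once 40 participants have completed mid-treatment assessments.
- Methodology on treatment fidelity names a general Satisfaction with Therapy Scale, alongside a scale for patients' experience of online EMDR.

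**The concern.** A hypothesis about two delivery modes needs, for each construct, a measure that can be obtained in both. Here the hypothesis covers both modes, while the instruments assigned to three of its constructs carry an app, a technology or online therapy in their names. A client treated face to face has no app or platform to rate.

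What is at stake is what the trial may conclude. Followed as written, it could report high usability and acceptance in both modes from scores that exist for one mode only. Alternatively, an in-person substitute could be picked after the data are seen. On safety, the formal outcome would be a perception score from the online arm, while the more informative adverse event data from both arms would sit outside the outcome list.

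**Working it through.** No arithmetic applies. The check sets each construct in hypothesis (i) against the measure named for it and asks whether that measure can be obtained from in-person clients.

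| Construct in hypothesis (i) | Measure in Secondary outcomes | Obtainable in person? | Relevant data elsewhere in the protocol |
|---|---|---|---|
| Feasibility | Retention rate; therapist adherence scale | Yes | Not needed |
| Usability | App usability questionnaire | No, judging by its name | None found |
| Acceptance | Technology acceptance questionnaire | No, judging by its name | Satisfaction with Therapy Scale, placed under treatment fidelity and not designated as the acceptance outcome |
| Technical operability | No separately named instrument | Not applicable | None found |
| Safety | Perceived online safety scale | No, judging by its name | Adverse events recorded for all participants and compared between arms at the first interim analysis |

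**Matching measures to constructs.** The list pairs five measures with four constructs. The natural reading gives feasibility the first two measures and each other construct one. Any other in-order assignment would still leave the last three measures specific to technology or online delivery.

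**Does the protocol support the name-based reading?** In part. Section {18a} speaks of three instruments that evaluate the online platform, and exactly three of the listed measures are technology-specific by name. It does not name its three, however, and it mentions feasibility and acceptability rather than usability or safety.

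**Does the phase matter?** Trial design {8} confines hypothesis testing to phase three, whereas Statistical methods {20a} describes the feasibility analysis (descriptive statistics and a one-sample t-test) under phase two. Study setting {9} delivers therapy both online and in person in each of these phases, so the mismatch arises in either.

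**Extent.** Three of the five listed measures are affected. If they are given in phase three and in-person clients cannot complete them, the clients without data number 80 / 2 = 40 at the 1:1 allocation. The protocol does not state which arm receives which scale, so this figure is conditional.

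**The case against.** The strongest reply is that the trial does collect information on in-person delivery, and much of this stands.

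- **Safety.** A reader might infer that safety cannot be tested in the in-person arm. The protocol does not support that. Adverse events are recorded and graded for everyone and compared between randomised arms. What remains is that the outcome list omits them and names only the online perception scale.
- **Objective 2 as a whole.** A reader might infer that the second objective cannot be answered for in-person delivery. That goes too far. The objective covers feasibility and acceptance, and retention and therapist adherence address feasibility in both arms. Only the acceptance part lacks a designated in-person measure, and the satisfaction scale could fill that gap.
- **A missing between-arm comparison.** Hypothesis (i) claims a high level of each construct in each mode, not a difference between modes. The absence of a randomised comparison of acceptability is therefore no failure against the stated hypothesis.
- **Inference from names.** The instruments are not reproduced, and the assessment schedule is a figure that is not available here. That in-person clients cannot complete the scales is a plausible inference, not an established fact.

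The reply does not remove the core. This is not detail that an article leaves to a fuller document: the article assigns instruments to constructs, and for usability and acceptance that assignment does not fit the reach of the hypothesis. A later analysis plan could not create in-person data from online-only scales.

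**Conclusion.** The point holds for usability and acceptance: the hypothesis claims both modes, and the designated scales appear to serve only the online one. For safety it holds in a weaker form: both arms can be assessed, but not through the outcome the plan names. Feasibility is not affected. Technical operability has no separately named measure and is by nature a property of the online platform.

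This is a mismatch of scope in secondary outcomes. It touches neither the primary endpoint nor the non-inferiority test nor the sample size. It should still be corrected, because it bears directly on what the trial may claim about in-person delivery.

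The conclusion rests on two assumptions: that the scales measure what their names say, with partial support from section {18a}; and that the in-person arm uses no app or platform, since none is described for it.

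**What to change.** 1. In hypothesis (i), restrict usability, technology acceptance, technical operability and perceived online safety to the online arm, reported descriptively.
2. In Secondary outcomes, list adverse event rates, as recorded under section {22}, as the safety outcome for both arms.
3. Confirm whether the Satisfaction with Therapy Scale is given in both arms. If so, designate it as the acceptance outcome for both. If not, limit the acceptance claim to the online arm, in hypothesis (i) and in the second objective.
4. Keep retention and therapist adherence as the feasibility measures for both arms.

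The cost is a documented protocol amendment and a registry update. Trial status reports that recruitment began on April 1, 2025, so the change falls during the trial and should be made before these outcomes are analysed. No new data collection is needed if the satisfaction scale is already given in both arms.
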